### Interventions

#### MY-PACE Program

Participants assigned to the MY‑PACE group receive 12 weekly, 90‑minute, live, supervised group sessions via Zoom (total virtual contact time: 18 hours), in addition to usual care. All participants are also instructed to practice the 20-minute audio-guided mindful walking exercise daily. Adherence is encouraged and documented through weekly phone calls or WhatsApp messages during the intervention period. Sessions are delivered to groups of approximately 20 participants by a certified yoga instructor with formal mindfulness qualifications. This protocol is adapted from a previously tested mindfulness yoga program implemented in a local population with PD [17,27] and comprises a combination of yoga movement, mindfulness meditation, and breathing techniques. This program emphasizes mobility and gait training, with a focus on mindful walking. Session content and structure are outlined in Multimedia Appendix 1.

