### Sample Size Calculation

Taking functional balance as the primary outcome, a meta‑analysis in individuals with PD reported a pooled mean difference of 3.64 (95% CI 2.06-5.22) points for resistance and balance training compared with control, corresponding to an estimated standardized effect size of Cohen *d*=0.66 [25], while a meta-analysis of cognitive-motor training in PD reported a standardized mean difference of 0.58 for balance outcomes compared with active or passive controls [26]. As this study will compare internally cued motor training with usual care, a conservative moderate effect size of 0.55 is assumed for the primary outcome. Using G*Power (version 3.1) for a 2‑arm parallel randomized controlled trial with a 2‑sided significance level of 0.05 and 80% power, 110 participants were required to detect an effect size of 0.55. Allowing for an anticipated attrition rate of 20%, a total sample size of 132 participants (66 per group) was recruited.

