### Procedure

Participants were recruited from local outpatient clinics and community organizations serving individuals with PD, including the Hong Kong Parkinson’s Disease Foundation, the Hong Kong Parkinson’s Disease Association, and the Community Rehabilitation Network. Study information and promotional materials were disseminated through online platforms and organizational networks. Potential participants were contacted by telephone or WhatsApp (Meta Platforms Inc) and screened for eligibility. Eligible individuals received a detailed explanation of the study via videoconference. Written informed consent was obtained in person prior to data collection. Following consent, baseline demographic and clinical assessments were conducted. All outcome assessments were performed during the participants’ self-reported medication “on” state to minimize the influence of motor fluctuations. Assessments were administered by trained research personnel who were blinded to group allocation. Participants were then randomly assigned in a 1:1 ratio to either the MY-PACE group (mindfulness-based, internally cued motor training) or the usual care group using a computer-generated randomization sequence. The allocation sequence was prepared by a researcher not involved in recruitment, intervention delivery, or outcome assessment. Group allocation was communicated to participants by an independent staff member to ensure allocation concealment. All outcome assessors remained blinded to group assignment throughout the study period.

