### Data Analysis

Data analysis will be performed using SPSS (version 28.0.1; IBM Corp) software following the intention-to-treat approach. Descriptive statistics will be used to summarize the sociodemographic characteristics and clinical background of all participants. The homogeneity of baseline characteristics between the 2 groups will be tested by the Pearson chi-squared test or Fisher exact test, as appropriate. Linear mixed-effect models will be used to assess the intervention effects on the primary and secondary outcomes, with time (as a continuous variable), group, and the group-by-time interaction included as independent variables. Linear contrasts will be used to obtain between-group differences. The normality of the residuals and random effects will be assessed using normal probability plots. Missing values will not be replaced because mixed-effect models can accommodate participants with at least 1 outcome measurement [37]. A 5% level of significance will be adopted, with all significance tests being 2-sided.

For the qualitative data, all audio-taped interviews will be transcribed verbatim and managed by NVivo (version 12.0; Lumivero LLC). Two experienced qualitative researchers will carefully and inductively review the transcripts. A 5-step thematic analysis will be adopted [38]. The coded units will be sorted into categories and subcategories and analyzed to identify recurrent themes and patterns. This qualitative data will enhance the interpretation of the quantitative findings and help identify the strengths and weaknesses of the intervention being tested. An audit trail will be maintained to ensure data credibility. The coded data will be compared to identify discrepancies, and any disagreements will be resolved through discussion.

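### MY-PACE is taught in about three or four classes in one arm only, but the sample size makes no allowance for class clustering and the described model names no class term; the effect depends on a class ICC that is not given.

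*Protocol article*

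**What the plan says.** **Delivery.** In the MY-PACE Program section, the intervention is twelve weekly live Zoom sessions of 90 minutes, and "Sessions are delivered to groups of approximately 20 participants by a certified yoga instructor with formal mindfulness qualifications". The Usual Care section gives controls routine outpatient services and a leaflet, with the programme offered only after the six-month study period. The Treatment Fidelity section refers to a single instructor.

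**Sample size.** The Sample Size Calculation section describes a G*Power calculation for a two-arm parallel trial: "a conservative moderate effect size of 0.55 is assumed for the primary outcome", and "110 participants were required to detect an effect size of 0.55" at two-sided 5% and 80% power. It continues: "Allowing for an anticipated attrition rate of 20%, a total sample size of 132 participants (66 per group) was recruited". It mentions no ICC or design effect.

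**Analysis.** The Data Analysis section specifies linear mixed-effects models "with time (as a continuous variable), group, and the group-by-time interaction included as independent variables". It refers later to checking the normality of random effects but does not say at which level they sit. No class term is named.

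**Timing.** The Results section reports that 132 participants are enrolled and that no outcome data have been analysed.

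**The concern.** Participants are randomised individually, but those in the MY-PACE arm are then taught together. People in the same class share the same live sessions, the same peers and the same dates, so their outcomes after treatment may be correlated. Controls have no such grouping. This is a partially nested design, with clustering in one arm only.

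The article itself suggests a mechanism. Its Discussion presents peer connection and real-time feedback as things the live group format preserves. An instructor effect is a weaker candidate. One person appears to teach every class, so that effect would be common to the whole arm and would not add variance between classes.

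If classes do differ, two separate things follow. An analysis that ignores class understates the standard error of the treatment effect and rejects too often. An analysis that allows for class has the right standard error but less power than the sample size section states.

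**Working it through.** **Inputs**
- d = 0.55, two-sided 5%, 80% power, 110 required, 132 recruited (66 per arm), 20% attrition: Sample Size Calculation.
- Class size about 20: MY-PACE Program. Number of classes K: 66/20 = 3.3, so 3 or 4. This is inferred, not stated.
- Class ICC: not given. Assumed values are 0, 0.01, 0.02 and 0.05.
- Evaluable at planned attrition: 66 × 0.8 = 52.8, taken as n = 53 per arm.

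**Reproducing the plan's figure.** For independent observations, 55 per arm gives 81.6% power by t test (82.2% by normal approximation). The exact minimum for 80% is 53 per arm, or 106 in total. The stated 110 is therefore a calculation for independent participants. The surplus of four would absorb a class ICC of only about 0.004 at class size 20.

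**Formulas** (outcome SD 1, equal classes, m = n/K)
- Design effect in the MY-PACE arm: DE = 1 + (m − 1) × ICC.
- Variance of the difference relative to independence: R = (DE + 1)/2.
- Power of a cluster-adjusted test, normal approximation: Φ(0.55/√(2/n)/√R − 1.96).
- Small-sample version: noncentral t with Satterthwaite df = (DE + 1)²/[DE²/(K − 1) + 1/(n − 1)].
- Type I error of a test that ignores class: 2[1 − Φ(1.96/√R)].

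**Worked case:** n = 53, K = 3, ICC 0.05. m = 17.67, DE = 1 + 16.67 × 0.05 = 1.83, R = 1.417, √R = 1.190. 0.55/√(2/53) = 2.831, and 2.831/1.190 − 1.96 = 0.419, so power is 66.2%. 1.96/1.190 = 1.647, so the type I error of the unadjusted test is 10.0%.

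**Results** (each cell: 3 classes / 4 classes)

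| n per arm | ICC | Adjusted power, normal | Adjusted power, Satterthwaite | Type I error, class ignored |
|---|---|---|---|---|
| 53 | 0 | 80.8% / 80.8% | 69.5% / 73.4% | 5.0% / 5.0% |
| 53 | 0.01 | 77.6% / 78.5% | 64.1% / 70.0% | 6.0% / 5.7% |
| 53 | 0.02 | 74.6% / 76.2% | 59.3% / 66.8% | 7.0% / 6.4% |
| 53 | 0.05 | 66.2% / 69.8% | 47.4% / 58.1% | 10.0% / 8.6% |
| 66 | 0 | 88.5% / 88.5% | 78.6% / 82.3% | 5.0% / 5.0% |
| 66 | 0.01 | 85.2% / 86.1% | 72.2% / 78.4% | 6.2% / 5.9% |
| 66 | 0.02 | 81.9% / 83.6% | 66.2% / 74.5% | 7.5% / 6.8% |
| 66 | 0.05 | 72.5% / 76.5% | 51.5% / 64.0% | 11.3% / 9.6% |

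The power columns and the error column belong to different analyses and should not be read as properties of one test. A simulation of the class-ignoring t test (40,000 runs per setting) at ICC 0.05 gave type I error of 8.6-9.8% at 53 per arm and 9.8-11.4% at 66. Its apparent power was 76-78% and 84%.

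**ICC at which adjusted power falls to 80%** (normal approximation). Power is 80% when 0.55/√(2/n)/√R = 2.80. This gives an ICC of about 0.003 at 53 per arm, 0.007-0.009 at 55, and 0.026-0.035 at 66. For n = 66 and K = 3: R = (3.1595/2.8016)² = 1.272, DE = 1.544, ICC = 0.544/21 = 0.026.

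**The case against.** A reader might infer that the stated 80% power and 5% error simply fail, or fail at any positive ICC. The documents do not support that. They give no class ICC, both figures hold at zero, and 80% survives small positive values, larger ones if attrition is low. At ICC 0.01 the error of an unadjusted test is only about 6%.

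A reader might also infer that the planned model certainly treats classmates as independent. The quoted list covers fixed effects, where a class random effect would not appear, and the level of the random effects is left open. A separate analysis plan, not shown, could define one. This objection stands for the model. It does not help the sample size, which is stated in full and has no clustering allowance.

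Other points reduce the likely ICC. A single instructor adds no between-class variance, daily practice is done alone at home, and the primary outcome is a performance test scored by blinded assessors. Nothing shows that calendar effects are confined to one arm. These are reasons to expect a small correlation, not to assume that it is zero.

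Finally, a class random effect estimated from three or four classes is costly as the primary model. The Satterthwaite column shows a substantial loss of power even at ICC 0. That is a good argument against making it compulsory as the primary analysis, and it shapes the fix.

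**Conclusion.** The concern holds in conditional form. The design is partially nested, the sample size ignores this, and the described model names no class term.

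At planned attrition, power of a cluster-adjusted test drops below 80% once the class ICC passes about 0.003, and is about 78% at 0.01, 75-76% at 0.02 and 66-70% at 0.05 by normal approximation. It is lower with small-sample df. With no attrition, 80% holds up to about 0.026-0.035 by normal approximation, but not at ICC 0.02 with Satterthwaite df. If class is ignored in the analysis, type I error is about 6% at ICC 0.01, 6-7.5% at 0.02 and 9-11% at 0.05.

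This rests on assumed ICCs, on three or four equal classes inferred from the class size, and on a single two-group comparison as in the sample size section. Baseline adjustment and repeated measures would change the absolute power but not the direction.

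**What to change.** Before any outcome analysis:

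1. Keep the class ID of each MY-PACE participant in the analysis dataset.
2. Prespecify, at least as a sensitivity analysis of the primary Berg Balance Scale comparison, a partially nested model: a class random effect in the MY-PACE arm only, each control as a singleton, with Satterthwaite or Kenward-Roger df. As baseline is measured before randomisation, the class effect belongs to T1 and T2.
3. Because three or four classes estimate the class variance poorly, add a table of the treatment effect and confidence interval with the ICC fixed at 0.01, 0.02 and 0.05.
4. Report the estimated class ICC and the actual number and size of classes.
5. State that the 80% power assumes zero class ICC, and give the conditional figures above.

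The cost is some added wording, one random term and one table. The price in the results is wider intervals in the cluster-adjusted analysis and an imprecise class variance. The documents do not say whether class membership has been recorded, so that should be confirmed first. No new participants are needed.

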#### Usual Care

The usual care group continues routine outpatient services and receives an educational leaflet on general fall prevention and FOG management. Participants in this group will be offered the MY-PACE program after completion of the 6‑month study period.

### Treatment Fidelity

Prior to intervention commencement, the instructor completed an 8‑hour training session covering protocol procedures and safety precautions, including a return demonstration to ensure adherence to the intervention manual. Treatment fidelity is evaluated through virtual on‑site observation conducted by an independent research assistant. Adherence to the protocol is assessed using a standardized observation checklist to determine whether all modules are delivered as specified.

### Outcome Measures

Assessments are conducted at baseline (T0), 1 week after intervention (T1), and 3 months after intervention (T2) for all participants.

#### Primary Outcome

Functional balance is measured using the Berg Balance Scale (BBS). The BBS comprises 14 items evaluating balance performance during common daily activities, each rated on a 5‑point scale (0-4), yielding a total score ranging from 0 to 56. Scores of 0 to 20 indicate severe balance impairment, 21 to 40 indicate moderate impairment, and 41 to 56 indicate good balance. The BBS demonstrates excellent interrater (intraclass correlation coefficient=0.98) and intrarater reliability (intraclass correlation coefficient=0.98) and has been validated in individuals with PD [28].

#### Secondary Outcomes

Functional mobility is assessed using a validated smartphone-based instrumental 3-meter Timed-Up-and-Go (TUG) test [17] via the US Food and Drug Administration–approved Mon4t Clinic (Montfort Brain Monitor Ltd) application [29]. A designated device is attached to the participant’s sternum using a flexible strap. Participants are instructed to sit on a chair with their hips positioned fully against the back of the seat. When the test starts, a countdown is heard, followed by an auditory and vibratory start cue. Participants are instructed to stand up, walk for 3 meters, turn around, walk back to the chair, and sit down. The total test time is recorded.

Gait patterns are assessed using a validated smartphone‑based 5‑meter instrumented TUG test via the Food and Drug Administration–approved Mon4t Clinic application. The device is positioned at the sternum as previously described. Participants complete 3 conditions: (1) a standard 5‑meter TUG test, in which they rise from a chair, walk 5 meters, turn, return, and sit down; (2) an obstacle 5‑meter TUG test, during which they walk 5 meters between 2 chairs spaced 24 inches apart before turning and returning to sit; and (3) a dual‑task 5‑meter TUG test. For the dual‑task condition, participants perform the 5‑meter TUG test while simultaneously completing a cognitive task involving serial subtraction performed continuously until the test is completed. Objective gait parameters, including step length, cadence, gait velocity, step-to-step variability, and postural sway, are extracted from the application.

Perceived balance confidence is measured in both medical “on” and “off” states using the Chinese version of the Activities‑Specific Balance Confidence Scale [30], a validated and reliable 16‑item instrument that evaluates individuals’ confidence in performing various indoor and outdoor activities. Each item is rated from 0% (no confidence) to 100% (complete confidence). Higher total scores indicate greater balance confidence.

Subjective experiences of FOG are assessed using the Chinese version of the FOG-Questionnaire [31]. The FOG‑Questionnaire consists of 6 items evaluating the severity and impact of freezing episodes on gait. Each item is rated on a 5‑point scale from 0 (absence of symptoms) to 4 (most severe), yielding a total score ranging from 0 to 24. Higher scores indicate more severe FOG.

PD-related motor symptoms are measured using the validated Movement Disorder Society–Unified Parkinson’s Disease Rating Scale (Chinese version) part III [32], which measures major PD motor symptoms, including tremor, rigidity, bradykinesia, gait, and postural instability. Higher scores indicate greater disease severity. The motor examination is conducted by qualified personnel with a Movement Disorder Society–Unified Parkinson’s Disease Rating Scale certificate.

Anxiety and depressive symptoms are measured using the validated Hospital Anxiety and Depression Scale (Chinese-Cantonese), a self-report questionnaire that consists of anxiety and depression subscales. Each subscale consists of 7 items, and each item is rated on a 4-point scale. A high score represents a high level of psychological distress. The Hospital Anxiety and Depression Scale has been suggested for use in populations with PD because somatic symptoms that may overlap with Parkinsonian manifestations are not assessed in this scale [33]. Additionally, the scale focuses on measuring the negative emotions related to anxiety and depression, which have been reported as the most prominent psychological factors in patients with PD.

Cognitive function and attention are measured using the Hong Kong Montreal Cognitive Assessment 5-min protocol, a validated tool for cognitive impairment in Chinese older adults that can be administered over the telephone. It consists of 4 subtests examining 5 cognitive domains, including attention, verbal learning and memory, executive functions or language, and orientation. Total scores range between 0 and 30. Patients with significant cognitive impairment are excluded using the cutoff scores based on age- and education-corrected normative data [23].

Mindfulness is measured using the validated 20-item Five-Facet Mindfulness Questionnaire (short-form; Chinese version) [34]. Using a 5-point Likert scale, 5 mindfulness domains are assessed, including observing, describing, acting with awareness, nonjudgment of inner experience, and nonreaction to inner experience.

HRQOL is assessed using the validated PD questionnaire-8 (Chinese version) [35,36]. With 8 items, the scale yields a summary index score capturing disease-specific HRQOL regarding mobility, activities of daily living, emotional well-being, social support, cognitions, communication, bodily discomfort, and stigma.

The incidence, reasons, and consequences of falls are assessed monthly. A fall is defined as “an unexpected event in which you come to rest on the ground, floor, or other lower level.” Participants are contacted monthly by a trained research assistant using a structured interview format. During each follow-up, participants are reminded of the standardized fall definition and asked the following standardized questions: (1) whether any falls occurred in the preceding month, (2) the number of falls, (3) the circumstances surrounding each fall, and (4) whether any injury or medical attention resulted. To reduce recall bias, participants are encouraged to record falls prospectively during the study period.

Sociodemographic data are collected using a self-report questionnaire, including age, gender, marital status, educational level, religiosity, and financial status. In addition, clinical data, including time since onset, history of comorbidities (eg, hypertension and diabetes mellitus), history of psychiatric disturbances, treatment and medication records, and history of rehabilitation service use, are documented and considered control variables in the data analysis.

### Ethical Considerations

This study complies with the ethical principles set forth in the Declaration of Helsinki. Approval was granted by the institutional review board of the University of Hong Kong–Hospital Authority Hong Kong West Cluster (UW 19-535) on September 18, 2019. The study objectives, voluntary participation, and participants’ rights—including the right to decline participation and withdraw at any time without any consequence—were communicated clearly both verbally and through a detailed information sheet. Participants are encouraged to ask questions and seek clarification about the study to ensure they fully understand their rights. Each participant is assigned a participant code to ensure anonymity, and no identifying information is included in the questionnaires. All collected data are securely stored and are accessible only to members of the research team. To enhance the protection of participants’ confidentiality, no identifiable information is included in the data files. All data will be destroyed 7 years after the study completion. Modest financial incentives (US $6.4, $6.4, and $12.8 at baseline, T1, and T2, respectively) will be provided to participants who completed the assessment interviews.

### Safety

Safety is of particular importance in individuals with PD, especially given the increased risk of falls. Appropriate measures are implemented to ensure participant safety during both exercise sessions and assessment time points. Participants identified as being at risk of falls are instructed to perform the live‑streamed MY‑PACE sessions in a safe environment, positioned next to a wall for support, with a stable chair placed nearby. Caregivers are encouraged to remain present during exercise sessions to provide additional supervision and assistance if necessary. Participants are instructed to immediately report any adverse events or discomfort related to the intervention to the research team. All adverse events are documented systematically, monitored throughout the study period, and followed by appropriate actions to ensure participant safety.

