### Aims and Hypotheses

This study aims to do the following:

Examine the effects of MY‑PACE, compared with usual care, on functional balance (primary outcome) and secondary outcomes, including functional mobility, balance confidence, freezing of gait (FOG) severity, motor symptoms, anxiety and depressive symptoms, cognitive function, mindfulness, HRQOL, and the incidence of falls over a 6‑month period in individuals with PDExplore participants’ experiences with MY‑PACE, including their practice of mindfulness yoga and factors influencing motivation, acceptability, and integration into daily life

It is hypothesized that participants with PD who receive the MY‑PACE intervention will demonstrate significantly greater improvements in functional balance at postintervention follow-up (T1) and at the 6‑month follow‑up (T2) compared with those receiving usual care. In addition, it is hypothesized that participants in the MY‑PACE group will show greater positive changes in secondary physical, psychological, and cognitive outcomes relative to the control group across the same time points.

The exploratory research question is as follows: What are participants’ experiences of using mindfulness yoga as a lifestyle intervention for balance management, particularly regarding perceived effects, perceived mechanisms of action (ie, how and why mindfulness may or may not work), and contextual factors influencing motivation, acceptability, and real‑life practice?

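### Adverse events other than falls are collected by self-report worded around relation to the intervention, so their capture is unlikely to be comparable between arms

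*Protocol article*

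**What the plan says.** The Safety section tells participants what to report: "Participants are instructed to immediately report any adverse events or discomfort related to the intervention to the research team". Its next sentence says that "All adverse events are documented systematically, monitored throughout the study period, and followed by appropriate actions to ensure participant safety". It gives no schedule and no question by which staff ask about adverse events.

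Falls are handled differently. Under Secondary Outcomes, "The incidence, reasons, and consequences of falls are assessed monthly", and "Participants are contacted monthly by a trained research assistant using a structured interview format". The four listed questions cover whether a fall occurred, how many, the circumstances, and "whether any injury or medical attention resulted". No arm restriction and no relatedness condition is attached. Aims and Hypotheses lists fall incidence as a secondary outcome for comparison with usual care.

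Staff contact differs by arm. The MY-PACE Program section describes 12 weekly live sessions and adherence "documented through weekly phone calls or WhatsApp messages during the intervention period". The Usual Care section describes routine outpatient services and a leaflet, with MY-PACE offered only after the 6-month study period.

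**The concern.** The collection rule that is printed depends on two things that differ by arm: whether a participant has an intervention to blame, and how often a participant speaks to the trial team. Both favour more reports from MY-PACE. Events such as pain, dizziness, strain or an injury without a fall could then appear more often in MY-PACE even if the true rates are equal.

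The relatedness wording also works in the other direction. An event that the programme did cause, but that the participant does not attribute to it, may never be reported. Comparing all events by arm is the usual protection against this, and it works only if both arms are asked in the same way.

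The intervention is home-based exercise in people whom the Safety section itself describes as at increased risk of falls. Much of the prescribed activity takes place outside the live classes, so a reader of the results will want a safety statement.

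**Working it through.** The article states no adverse event figure, so there is none to reproduce. The check sets the sections side by side and then illustrates the possible size.

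**1. Routes by type of event**

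| Event | Route described | Same in both arms? |
|---|---|---|
| Falls, fall injury, medical attention after a fall | Monthly structured call with standard questions (Secondary Outcomes) | Yes: no arm restriction, no relatedness condition |
| Any other adverse event | Participant self-report (Safety) | Not secured: worded around relation to the intervention, which only MY-PACE receives during follow-up |

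**2. Contacts at which an event could be mentioned, over 6 months**

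- MY-PACE: 12 sessions + about 12 weekly calls or messages + about 6 monthly calls = about 30.
- Usual care: about 6 monthly calls.
- T1 and T2 assessments add 2 in each arm, giving about 32 against 8.

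The weekly contacts are described for adherence, not for harms. They are opportunities to volunteer an event, not a collection procedure.

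**3. Prescribed exposure in MY-PACE**

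- Daily audio-guided walking: 12 weeks × 7 days × 20 min = 1,680 min = 28 h.
- Live sessions: 12 × 90 min = 1,080 min = 18 h.

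If followed as instructed, more of the practice lies outside the live sessions than in them. This bears on why non-fall events matter. It does not measure unequal capture.

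**4. Illustration of the bias (assumed inputs)**

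From the article: n = 66 per arm, two-sided 5% level. Assumed, because the article gives neither: an equal true risk p of at least one non-fall event in both arms, full capture in MY-PACE, and a fraction c captured in control. The recorded risks are then p₁ = p and p₂ = c·p.

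The approximate chance of a significant excess in MY-PACE is Φ[(p₁ − p₂ − 1.96·SE₀)/SE₁], where SE₀ = √(2·p̄(1 − p̄)/n), p̄ = (p₁ + p₂)/2, and SE₁ = √([p₁(1 − p₁) + p₂(1 − p₂)]/n).

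For p = 0.20 and c = 0.50: p₁ = 0.20, p₂ = 0.10, p̄ = 0.15, SE₀ = 0.0622, SE₁ = 0.0615. Then (0.10 − 1.96 × 0.0622)/0.0615 ≈ −0.35, and Φ ≈ 0.36. Expected participants with a recorded event are 66 × 0.20 = 13.2 in MY-PACE and 66 × 0.10 = 6.6 in control.

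| True risk in both arms | c = 75% | c = 50% | c = 25% |
|---|---|---|---|
| 10% | 7% | 19% | 43% |
| 20% | 11% | 36% | 75% |
| 30% | 16% | 54% | 92% |

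The true risk is the same in both arms throughout, so every significant result in this table would be false. The table covers only under-capture in control. It does not model events lost because the participant thinks them unrelated.

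**The case against.** The strongest reply has five parts.

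- **Falls are actively collected.** The main harm named in the Safety section is solicited monthly. This stands. A reader might infer that all adverse events rest on spontaneous reporting and that no by-arm safety statement is possible. The Secondary Outcomes section contradicts that for falls, fall injuries and resulting medical attention.
- **The sentence is ambiguous.** The relatedness phrase may qualify only discomfort, and the following sentence ("All adverse events are documented systematically, monitored throughout the study period") fits that reading. This also stands, but it does not remove the point. On the milder reading the route is still unsolicited self-report with unequal contact, and the ambiguity is itself a reason to reword.
- **The article is condensed.** Adverse event forms, seriousness grading, relatedness assignment and tabulation may stand in the full protocol, and their absence here is no finding. That is accepted. The point concerns the rule that the article does print.
- **No comparison of non-fall events is promised.** The aims list only falls among possible harms, and the Data Analysis section names no adverse event comparison. This limits the point to what may be concluded later.
- **The size is unknown.** A reader might infer that almost no control events would be recorded whatever the true rate. The article gives no capture fraction, and the instruction is addressed to participants in general, so under-capture is as far as the text goes.

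**Conclusion.** The point holds for adverse events other than falls. As printed, their collection is passive and worded around an intervention that one arm does not receive during follow-up, and it is accompanied by much more staff contact in the other arm. A by-arm comparison of these events would probably be biased towards apparent excess harm in MY-PACE, while harm that participants do not attribute to the programme could be missed.

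The size cannot be stated. Across the assumed risks of 10% to 30% and control capture of 75% to 25%, the false-positive chance runs from about 7% to 92%, which shows direction and range only. The conclusion assumes that the full protocol contains no solicited question common to both arms; if it does, only the wording of the article needs correcting.

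The sentence on systematic documentation is not shown to be false, but documentation can be no more complete than the reports that feed it. The comparison of falls and fall injuries is unaffected.

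**What to change.** Reword the Safety section so that all adverse events, whatever their perceived relation to the intervention, are asked about with the same open question in both arms within the existing monthly call. Report events volunteered through the MY-PACE sessions and weekly contacts separately from those elicited by the common question.

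All 132 participants are enrolled, and the article does not say whether follow-up is complete. If the calls have ended, limit by-arm safety conclusions to falls and fall injuries, and report other events descriptively with the difference in ascertainment stated. If they are still running, the new question covers only the remaining calls, and the report should say from when it was asked.

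The cost is one question on a call that already takes place, with slightly longer calls and more minor events to record. The fallback costs only wording, and the article says that no outcome analysis has yet been done.
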